## Abstract

Mental and cognitive disorders (MCD) negatively affect the incidence and prognosis of coronary heart disease (CHD). Medical guidelines recommend the appropriate management of comorbid MCD in patients with CHD, yet there is evidence that the implementation in primary care is not always adequate. We present the protocol for a pilot study that aims to develop a minimally invasive intervention and evaluate its feasibility in the primary care setting to improve the identification and management of comorbid MCD in patients with CHD. The study consists of two consecutive parts and will be carried out in Cologne, Germany. Part 1 comprises the development and tailoring of the intervention, which is guided by qualitative interviews with primary care physicians (PCPs, *n* = 10), patients with CHD and MCD and patient representatives (*n* = 10). Part II focuses on the implementation and evaluation of the intervention in *n* = 10 PCP offices. Changes in PCP behaviour will be analysed by comparing routine data in the practice management system six months before and six months after study participation. In addition, we will explore the influence of organisational characteristics and perform a socio-economic impact assessment. The outcomes of this mixed-method study will inform the feasibility of a PCP-based intervention to improve quality of care in patients with CHD and comorbid MCD.

## 1. Introduction

Coronary heart disease (CHD) ranks among the highest drivers of global disease burden among all age groups, but specifically in the age group of 50 years and older [1]. To this date, it is considered the leading cause of mortality in Germany [2]. Mental and cognitive disorders (MCD) are among the top causes for global disease burden [1], and they also negatively affect the incidence and prognosis of CHD. The prevalence of depression is 15–30% among patients with CHD and therefore higher compared to the general public [3]. There is strong evidence that depression and anxiety are risk factors for negative disease prognosis and mortality [3,4,5], and they negatively impact quality of life [6] and reduce adherence to necessary lifestyle changes and treatment [7]. In addition, interactions between cognitive impairment or dementia and CHD have been observed. On the one hand, cognitive deficits are considered risk factors for non-adherence to therapy [8] and may therefore impair disease prognosis, while on the other hand, CHD has been shown to increase the risk of subsequent dementia [9]. Current guidelines therefore recommend appropriate diagnosis and treatment of comorbid MCD in patients with CHD [4,7,8,10].

The identification and management of both mental and cognitive disorders are common responsibilities of primary care physicians (PCP). However, there is evidence that guideline recommendations are not adequately implemented in primary care. A meta-analysis on the ability of PCPs to diagnose depression indicated that PCPs showed a diagnostic sensitivity of 47.3–50.1%, while the rate of correctly identified non-depressed individuals was higher (81.3%) [11]. This is in line with data from the “Quality of health care with regard to detection and treatment of mental disorders in patients with coronary heart disease” (MenDis-CHD) study [12]. That study showed that, out of 102 patients who were diagnosed with a mental disorder by the study team, 51% had not yet received a diagnosis from their physician [13]. Several causes for underdiagnoses of dementia in the primary care setting have been identified, including lack of adequate training, fear of stigma, and time and resource constraints [14,15,16]. However, while identification of symptoms is important and the premise for subsequent actions, it needs to be followed up by adequate management and treatment procedures. Moreover, quality of care strongly relies on how MCDs are addressed within the patient–carer relationship.

For this pilot study, we aim to develop and test the feasibility of an intervention to improve the identification and management of MCD in patients with CHD in the primary care setting. The rationale is largely based on results from the cross-sectional MenDis-CHD study [12,13,17]. It is part of the interdisciplinary Cologne Research and Development Network (CoRe-Net), a competence network of practice and research for the model region of Cologne [18]. The network is funded by the German Federal Ministry of Education and Research (BMBF) and based on the value-based health care approach [19,20,21].

## 2. Materials and Methods

### 2.1. Study Setting

This study is part of the CoRe-Net research projects MenDis-CHD II, a study on quality of care in diagnosis and therapy of MCD in CHD, and OrgValue II, a study on characteristics of value-based care from the perspective of care institutions. It consists of two consecutive parts. Part I aims to develop a minimally invasive intervention to improve identification and management of MCD in CHD patients in the primary care setting. Additionally, potential determinants of implementation in PCP offices will be identified. In this context, “minimally invasive” refers to an intervention that hardly interferes with routine care practice and is designed to be time- and cost-efficient. The intervention will then be implemented and evaluated in PCP offices in Cologne, Germany and surrounding suburban municipalities in part II of the study. The total duration of Part II is twelve months, divided into a six-month pre-intervention observation period and a six-month intervention period. Our aims are to evaluate the feasibility of the intervention and, if given, assess whether the intervention changes PCPs’ management of CHD patients.

#### 2.1.1. Part I: Intervention Development and Tailoring

**Participants.** Interviews with PCPs in Cologne (*n* = 10), patients with CHD and MCD and patient representatives (i.e., representatives of patient organisations and self-help groups, *n* = 10) will be conducted to tailor and adapt the minimally invasive intervention and develop an implementation programme. It is assumed that information saturation is reached at about 10 interviews per group.

Inclusion criteria:

PCPs:Office located in Cologne or surrounding suburban municipalities

Patients:Diagnosis of CHD and comorbid MCD diseaseProficient in the German language≥18 years oldAble to provide written informed consent

Patient representatives:Proficient in the German language≥18 years oldAble to provide written informed consent

**Recruitment.** PCPs will be recruited via multiple channels. We will contact participants of PCP symposia organised by the University Hospital Cologne who consented to be contacted via e-mail. In addition, PCPs in Cologne and surrounding suburban municipalities will be contacted by phone via their publicly accessible contact information. Patient recruitment will be based on the MenDis-CHD I patient sample. Patient representatives will be recruited via the CoRe-Net network.

**Intervention development.** The overall aim of the intervention is to enhance awareness of mental and cognitive symptoms related to CHD in PCPs and patients and thereby stimulate improved diagnosis and management. The intervention will be composed of different elements: A trigger question, screening tests, information material for patients and PCPs and a training course for PCPs. The design of the intervention elements will be tailored to the PCPs’ needs and preferences and take into consideration the limited time resources available in PCP offices.

Trigger question: The trigger question will be adapted from the 12-month Surprise Question (SQ-12) known from palliative care research (“Would I be surprised if this patient died in the next 12 months?”) [22,23,24,25,26,27,28]. The SQ-12 has originally been designed to identify individuals eligible for palliative care and prompt treatment decisions. It will be adapted to fit our research question (“Would I be surprised if my patient had a mental or cognitive disorder?”). Based on previous experiences with the SQ-12, we assume that the focus of the question on surprise will stimulate reflection in the decision-making process and challenge routinised assumptions and patterns of behaviour. Therefore, PCPs should ask themselves the trigger question for each patient with CHD. As a result, we expect it to trigger consecutive actions as described in Figure 1, which are in line with recent diagnostic guideline recommendations for the identification and management of MCD [8,10,29,30,31]. PCPs should either confirm their assumption of the presence of MCD or actively approach uncertainty by using screening methods and following up with further diagnostics, therapeutic actions and information for the patients, depending on the screening result.

Booklet and screening material: In addition to the trigger question, a booklet will be designed for the PCPs participating in the study. It will include detailed information on the latest guideline recommendations regarding the detection of and care for MCD in patients with CHD and further assistance in dealing with the intervention. Additionally, PCPs will be provided with screening tools for time-efficient identification of potential cognitive difficulties and depressive or anxiety symptoms. Screening for depression or anxiety will be initiated by an open question on how patients are currently feeling, followed by the PHQ-4 as a brief screening scale with two items on depression and two items on anxiety [32], and another open question on potential further mental health problems. Screening for cognitive impairment will consist of a question on subjectively perceived cognitive decline and worries associated with it. In addition, the Six-Item-Screener is proposed as an easy-to-use screening tool that can be completed in about one minute and followed up by more detailed cognitive tests if necessary [33].

Training course: A training course for PCPs will be designed to increase knowledge and raise awareness for the common comorbidity of CHD and MCD. Furthermore, the training course will serve to familiarise the PCPs with the study materials. The training course will be led by senior investigators (FJ, CA) who are specialists in psychosomatic medicine and psychiatry and have longstanding expertise in CHD and PCP research. To harmonise the training course and ensure reliability, a presentation will be developed that serves as a guideline. Details of the training course, such as length, specific contents or the participation of staff, will be tailored to the results of the qualitative interviews.

Question prompt sheets: We will develop a question prompt sheet (QPS) for patients. A QPS provides adequate support for communication between patients and providers. Its use can empower patients to take up an active role in communication with their PCPs, ask questions and thus receive more information. This increases patient knowledge and has a positive effect on patient satisfaction and the physician-patient relationship [34,35]. It also reduces potential patient anxiety without increasing the consultation time [35,36,37]. The QPS will provide evidence-based information about the comorbidity of CHD and MCD, examples of relevant questions, space for personal notes and information on further resources or points of contact.

#### 2.1.2. Part II: Intervention Implementation

**Participants.** For the implementation of the minimally invasive intervention designed in Part I, we intend to enrol *n* = 10 PCP offices (single or group practices). The sample size is based on calculations of the number of patients with CHD per practice per quarter. Based on previous reports, we assume that the number of patients per quarter per PCP will be 900 [38]. Data from the DETECT study on 55,518 patients in German primary care showed that 12.4% were diagnosed with CHD [39]. As a conservative measure, we decided on an estimate of 10% CHD patients, yielding *n* = 90 CHD patients per PCP per quarter. Multiplied by the number of PCP offices (*n* = 10), we expect 900 CHD patients per quarter, providing us with 1800 cases in the six-month pre-intervention observation period and 1800 cases in the six-month intervention period. To control for the influence of gender, we aim to balance recruitment of PCPs.

Inclusion criteria:Single or group PCP office in Cologne or the surrounding suburban municipalities

Exclusion criteria:Advanced training in basic psychosomatic careSpecialist additional qualification of psychotherapyParticipation in an interview in Part I

**Recruitment.** Recruitment strategies will focus on several channels, including presentation of the project at PCP events or symposia, recruitment via CoRe-Net, and invitation e-mails or letters to local PCP networks and PCP offices associated with the University Hospital Cologne.

**Intervention implementation.** PCPs will be invited to a training course as developed in Part I of the study. They will be encouraged to use the study material as described above during the six-month intervention period to aid them in identifying and managing CHD patients with potential MCD. However, we will not monitor usage and will instead emphasise that the intervention should be implemented in accordance with the PCPs’ routine work structure. By doing so, we aim to stay close to a “real-world setting” to analyse feasibility and increase generalisability of the results. After completing the intervention period, each PCP will be interviewed to assess their experiences and evaluate the feasibility of the intervention.

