### 2.2. Outcomes

#### 2.2.1. Primary Outcome

The primary objective of this study is to evaluate the feasibility of the intervention in the PCP setting. Using a qualitative approach, we will evaluate feasibility and acceptance as well as barriers and facilitators of the implementation. Routine care data will quantitatively inform about the number of patients with CHD potentially reached by the minimally invasive intervention. In addition, we will assess recruitment success and the rate of study completion.

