### 2.5. Data Analysis

Data analysis will be based on a combination of quantitative and qualitative analysis methods. The transcripts of the interviews in Parts I and II will be entered into MAXQDA software (VERBI GmbH, Berlin, Germany) and analysed following Miles and Huberman [42]. The software program MAXQDA will be used for the qualitative data analysis and supports the systematic evaluation and interpretation of the transcript. Qualitative content analysis will be chosen to explore the unique perspectives of the participants and to systematically extract the content to a descriptive level. To provide validity of data interpretation, transcripts will be independently coded by two researchers. A coding framework will be developed that combines deductive and inductive approaches. The deductive approach will draw on extant concepts for implementation of patient-centred care [43] as well as the Consolidated Framework for Implementation Research [44].

Descriptive and explorative methods will be used to analyse the quantitative routine data. To investigate the influence of the intervention on PCP behaviour, we will conduct repeated measures analyses to compare the frequency of diagnostic and therapeutic actions, referrals and medication prescription before and after the training course. In this context, the influence of organisational characteristics as well as the intervention adherence, as reported in the interviews, will be taken into consideration. In addition, we will record and analyse reasons for dropout or non-adherence to the study procedures. Data from PCP offices will be included in the analysis if a minimum of 80% (≥20 weeks) of the intervention phase has been completed before dropout. To reduce the risk of dropout, regular check-ins with the PCP offices will be carried out via e-mail or phone.

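### The feasibility interview and the 80% cut both condition on retention, so the qualitative part of the primary outcome and the routine-data results rest on offices that stayed

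*Protocol article*

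**What the plan says.** Section 2.2.1 makes feasibility the primary objective and names several components. The first is qualitative: "Using a qualitative approach, we will evaluate feasibility and acceptance as well as barriers and facilitators of the implementation". The second is a count: "Routine care data will quantitatively inform about the number of patients with CHD potentially reached by the minimally invasive intervention". Recruitment success and the rate of study completion are added to these.

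The qualitative component comes from the Part II interviews, which Section 2.1.2 times as follows: "After completing the intervention period, each PCP will be interviewed to assess their experiences and evaluate the feasibility of the intervention". The article describes no interview for a PCP who leaves before that point. The same section says that use of the material will not be monitored. Section 2.5 takes intervention adherence from what PCPs report in the interviews.

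Section 2.5 also sets an inclusion rule for offices that drop out: "Data from PCP offices will be included in the analysis if a minimum of 80% (≥20 weeks) of the intervention phase has been completed". It stands in the paragraph on quantitative routine data and does not say whether it reaches interview data or the count of patients reached. The same paragraph provides for reasons for dropout or non-adherence to be recorded and analysed, and for regular check-ins with the offices.

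Section 2.3 describes one routine-data export per office at the end of the intervention phase, reaching back over the preceding twelve months.

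**The concern.** A PCP who gives up because the intervention does not fit the practice is among the best informants on barriers. As written, that PCP has no stated place in the interviews, and the office's routine data are discarded if it left before week 20. If leaving is related to poor fit, acceptance will look better and barriers fewer than they were across all trained offices, and the before-after change will describe only offices that persisted.

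Three features of this study raise the stakes:

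- With no monitoring of use, the interview is the named source on adherence. A PCP without one leaves a gap there too.
- Section 2.1 makes the assessment of change in PCP management conditional on feasibility being given, so a favourable tilt in the feasibility evidence makes that step easier to reach.
- The Discussion says the results are to guide a subsequent RCT, and Section 2.1.2 wants to stay close to routine practice for the sake of generalisability. Selection on retention works against both.

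**Working it through.** **1. What the rules do to an office, by when it stops**

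| Office stops | Interview stated? | Routine data analysed? | Dropout visible elsewhere? |
|---|---|---|---|
| Does not stop early | Yes | Yes | Not applicable |
| From week 20 but before the end | No | Yes | Completion rate, recorded reason |
| Before week 20 | No | No | Completion rate, recorded reason |

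The middle row is a gap of its own. Such an office enters the before-after analysis, which is meant to take account of adherence as reported in the interviews, yet no interview is stated for it.

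**2. The plan's own case numbers**

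Inputs from Section 2.1.2: "we assume that the number of patients per quarter per PCP will be 900"; "we decided on an estimate of 10% CHD patients, yielding *n* = 90 CHD patients per PCP per quarter"; 10 offices; two quarters per period.

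- CHD patients per PCP per quarter: 900 × 0.10 = 90.
- All offices, per quarter: 90 × 10 = 900.
- Per six-month period: 900 × 2 = 1800. This reproduces the article's figure. It counts one PCP per office and allows for no dropout.
- One office per period: 90 × 2 = 180, which is 180/1800 = 10%.

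**3. What the cut removes**

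The rule excludes the office, so both of its periods go. If d of 10 offices stop before week 20, cases per period are 1800 − 180d:

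| Offices excluded | Offices analysed | Cases per period |
|---|---|---|
| 1 | 9 | 1620 |
| 2 | 8 | 1440 |
| 3 | 7 | 1260 |
| 4 | 6 | 1080 |

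**4. How likely a loss is**

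The article gives no dropout rate, so a range is assumed, with offices independent. P(at least one of 10 lost) = 1 − (1 − p)^10:

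- p = 10%: 1 − 0.9^10 = 65%
- p = 20%: 1 − 0.8^10 = 89%
- p = 30%: 1 − 0.7^10 = 97%

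**5. The cut against its own figure**

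Taking six months as about 26 weeks, 80% is 0.8 × 26 = 20.8 weeks, and 20 weeks is 20/26 = 76.9%. The two agree exactly only for a 25-week phase. This is a small separate point.

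**6. What cannot be computed**

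The size of any bias in the feasibility finding has no number. Interviews receive qualitative content analysis, and the article defines no proportion of PCPs who rate the intervention feasible.

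**The case against.** A reader might infer that the whole primary outcome comes from offices where the intervention worked. The article does not support that, for four reasons, all of which stand.

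- The rate of study completion is part of the primary outcome and reflects the offices that leave. If three of ten left, 70% completion would be reported together with the recorded reasons.
- The cut is on time in the study, not on use or effect. An office that stays six months and hardly uses the material is interviewed and analysed, so barriers and non-use can be heard from retained offices.
- The 80% sentence belongs to the routine-data paragraph, and the interview analysis in the paragraph before has no such cut. On the natural reading it governs the secondary before-after comparison and, at most, the reach count within the primary outcome.
- Section 2.1.2 says that each PCP will be interviewed and gives a time. It does not bar an interview with someone who leaves, and a full protocol may describe how dropout reasons are obtained.

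It can be added that this is an exploratory, uncontrolled pilot that declares its limits, and that some offices will leave for reasons unrelated to the intervention.

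These points narrow the concern but do not remove it. A recorded reason for leaving is not the semi-structured interview of Section 2.3, which explores barriers and facilitators in depth. The timing of the interview and the exclusion of offices below 80% are stated rules rather than omitted detail, and both select on retention.

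**Conclusion.** The concern holds in a limited form. The qualitative part of the primary outcome (acceptance, barriers, facilitators), the adherence information and the before-after comparison rest on retained offices, as does the reach count if the cut applies to it. They may therefore look too favourable. Recruitment success, the completion rate and the analysed dropout reasons are not affected in this way.

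The direction rests on the assumption that early leaving is related to poor fit. If offices leave for unrelated reasons, the cost is mainly lost information. That loss is 10% of expected cases per excluded office, assuming one PCP per office and equal office size. With only ten offices, losing at least one is more likely than not even at an assumed 10% dropout.

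The change is worth making because it is cheap, and because an interview missed at dropout may not be recoverable.

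**What to change.** **Section 2.1.2.** State that every PCP who received the training is offered the interview at the end of the intervention period or at dropout, whichever comes first.

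**Section 2.5.**

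- State that the 80% cut does not apply to interview data or to any feasibility outcome, including the number of patients reached.
- Analyse routine data from all trained offices as rates over observed time, up to dropout or, with consent, to month 6. The retrospective export in Section 2.3 makes this possible.
- Keep the set with at least 80% completed as a sensitivity analysis, and express its threshold so that the percentage and the number of weeks agree.

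**Cost.** This is mainly wording, and the number of interviews does not exceed those already planned. Some early leavers will refuse the interview or the export. Using data after dropout needs consent, and the double-pseudonymised data flow in Section 2.4 must accommodate offices that leave early. Partial windows need a rate denominator. Refusals should be reported, so that the remaining selection can be seen.
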